### Assessing association with mortality outcomes

Time-to-event analyses will be used to estimate the association between delivery and trauma-to-CRI time with mortality outcomes. This approach allows us to (1) systematically follow a representative cohort of injured individuals that are alive at the initial request for medical attention with moderate to high baseline risks, and (2) produce valid estimates of the timeliness and effectiveness of the urgent care initiated within the regional trauma system for these individuals [57]. Multivariable Cox proportional hazards models with a time-dependent covariate for CRI will be used to study the effect of receiving CRI during different time periods post-injury (e.g., 0–2, 2–12, > 12 h). We will assess model fit and the proportional hazards assumption. We will consider alternative model specifications as necessary, including a left truncated Cox proportional hazards model [58, 59], joint modelling of CRI and death [60–62], and estimating the survivor average causal effect (SACE) [63–66].

The secondary objective of assessing the effect of the delivery and timing of individual resuscitative interventions that occur during clinical course will be evaluated using similar models. Some interventions are injury-specific, and thus analysis will be performed in appropriate subgroups (e.g., by injury type and injury severity).

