### Variables, outcomes, and study measures

Epidemiologic information will be collected for each study participant for their entire clinical course at all associated study sites, including: patient demographic information (e.g., age, sex, race, and comorbidities); injury details (e.g., time, type, and intent); facility data (e.g., hospital name, trauma level, clinician qualifications, units of care); clinical data (e.g., vital signs, medications administered, critical interventions, operations performed); and, trauma system process (e.g., key dates and times [51]). Table 2 describes the exposures, predictors, and outcomes of interest in the EpiC study.

**Table 2 Tab2:** Key EpiC Study Exposure, Predictors, and Outcome Measures

Exposures	Definition	Variable Type	Data Source
1^O—^Critical resuscitative interventions (CRI)	Prehospital and in-hospital resuscitative interventions or therapeutics, delivered for the patient’s traumatic injury (e.g., thoracostomy for tension pneumothorax), within the first 24 h post-injury	Binary	EMS and/or Hospital
1^O^—Trauma-to-CRI time	Duration of time from injury to receiving a critical resuscitative intervention for the dominant injury	Continuous	EMS, Hospital, and/or Pathology

Predictors	Definition	Variable Type	Data Source
Age	Span of years lived at the time of injury	Continuous	EMS, Hospital, or Pathology
Sex	Biological sex given at birth	Categorical	EMS, Hospital, or Pathology
Comorbidities	One or more pre-existing disease or conditions present in the patient that are trauma-relevant chronic conditions (e.g., bleeding disorder)	Binary	EMS or Hospital
Socioeconomic status	Based on hospital insurance status	Categorical	Hospital
Mechanism of injury	Main force that created the injury or how injury was inflicted (e.g., firearm, Struck/hit, stabbing or cut, vehicular injury, fall, thermal, choking/hanging, iatrogenic, other)	Categorical	EMS, Hospital, or Pathology
Provider level	Health care provider qualifications (e.g., rank of EMS provider, type of doctor)	Categorical	EMS
Injury severity	ISS calculated as the sum of squares of 3 worst AIS scores. Low (< 12) or high (≥ 12)	Continuous, Binary	EMS, Hospital, or Pathology

Outcomes	Definition	Variable Type	Data Source
1^O—^Ambulance death or 7-day in-hospital mortality	All-cause mortality in the ambulance or within the hospital in the first 7-days post-injury	Time-to-event	EMS, Hospital, or Pathology

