## Statistical methods

Descriptive statistics will be estimated for all demographic, injury, facility, clinical, and systems process fields. Multivariable models will adjust for characteristics at the patient-level (e.g., age, sex, race, comorbidities, socio-economic status, injury mechanism, injury severity index) and provider-level (e.g., specialist trauma surgeon, general medical officer, advanced prehospital provider), as described in Table 2. Due to the small number of hospitals, site will be adjusted for as a fixed effect.

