### Power calculation

Based on a conservative estimate from the smallest hospital, we assume an average of 3,600 cases from each of the four hospitals in a 4-year period. Thus, we anticipate a total sample size of 14,400 cases over the study period. We assume that 30% of cases have an average trauma-to-CRI time within 2 h of injury and an average 7-day mortality of 10% for the primary mortality outcome. From a Cox proportional hazards regression, with 80% power (alpha = 0.05, two-sided) we can detect a hazard ratio of 0.85 for trauma-to-CRI time within the first 2 h versus not. For the morbidity outcomes, we present the power calculation for a continuous outcome (organ failure), and a binary outcome (wound infection). For the continuous outcome of organ failure, assuming the standard deviation of the SOFA score is 4 [71], with 80% power (alpha = 0.05) we can detect a mean decrease in score of 0.20 in those with trauma-to-CRI time within the first 2 h versus not, which corresponds to a standardized effect size of 0.05. For the binary outcome indicating whether a wound infection occurred, if 10% of cases with a trauma-to-CRI time within 2 h have a wound infection, with 80% power (alpha = 0.05, two-sided) we can detect an odds ratio of 0.84 for trauma-to-CRI time within 2 h versus not.

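### The mortality model updates CRI over time but names no time-updated clinical status, so deterioration after injury or arrival can confound both the delivery and the timing hazard ratios

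*Protocol article*

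**What the plan says.** Under Assessing association with mortality outcomes, the article plans "Multivariable Cox proportional hazards models with a time-dependent covariate for CRI" to study "the effect of receiving CRI during different time periods post-injury (e.g., 0–2, 2–12, > 12 h". The same section claims validity for the resulting estimates of how timely and effective care is.

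Under Statistical methods, "Multivariable models will adjust for characteristics at the patient-level" and the provider level, with reference to Table 2; site enters as a fixed effect. The named variables are age, sex, race, comorbidities, socio-economic status, mechanism, injury severity and provider level. None is described as updated over time. The severity measure is the ISS, which is anatomical. No vital sign or consciousness score is named as a covariate.

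The data are broader than the model: "Epidemiologic information will be collected for each study participant for their entire clinical course at all associated study sites", and the clinical data listed there include vital signs.

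Three alternatives are to be considered if needed: a left-truncated Cox model, joint modelling of CRI and death, and the survivor average causal effect. Inverse-probability weighting appears only in the morbidity section, where it handles censoring by death. The Limitations section does not mention confounding by indication.

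**The concern.** CRI counts as exposure if given at any time in the first 24 h after injury. A patient not yet treated at 2 h or 12 h may then be treated because his or her condition has worsened, and that worsening also predicts death. A model that updates the exposure but not the clinical state behind it credits the excess deaths to CRI. ISS does not carry this information, and first vital signs carry only part of it.

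Both parts of the first objective, delivery and timeliness, rest on these hazard ratios. The design aims at a modest effect, so modest confounding is enough to remove or mimic it. A true 0.85 is read as 1.00 if confounding multiplies it by 1/0.85 = 1.18.

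**Working it through.** **1. The plan's own figure.** Inputs from Power calculation: "we anticipate a total sample size of 14,400 cases over the study period", "30% of cases have an average trauma-to-CRI time within 2 h of injury" and "an average 7-day mortality of 10% for the primary mortality outcome".

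- Expected deaths: 14,400 × 0.10 = 1,440.
- Schoenfeld: deaths = (1.960 + 0.842)² / [0.3 × 0.7 × (ln 0.85)²] = 7.849 / (0.21 × 0.02641) ≈ 1,416.
- With 1,440 deaths, power is 80.7% and the detectable hazard ratio is exp(−√(7.849 / (0.21 × 1,440))) = 0.851.

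The stated 0.85 is reproduced and serves as the yardstick.

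**2. What the article does not give.** It does not say how strongly deterioration triggers CRI or predicts death. Every size below is therefore an assumption, shown as a range.

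**3. Simulation A: CRI works equally well in every band (true HR 0.70).** Assumed: 14,400 patients, 11% 7-day mortality, 27% treated within 2 h, 50% treated in all. Physiology drifts hourly (SD 0.2) for 24 h and raises both CRI initiation and death (coefficient 0.6). There were 14 replicates, with Monte Carlo SE of the mean log HR about 0.02–0.03.

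| Adjustment | 0–2 h | 2–12 h | >12 h |
|---|---|---|---|
| Anatomical-type baseline severity | 1.09 | 1.10 | 1.11 |
| Plus first physiology | 0.76 | 0.83 | 0.91 |
| Weights from time-updated physiology | 0.71 | 0.72 | 0.74 |

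The first row is closest to the plan. It is inflated by 1.09/0.70 = 1.56 to 1.11/0.70 = 1.59 and is flat across bands. With first physiology added, the early/late ratio is 0.76/0.91 = 0.84 where the truth is 1. That second row becomes 0.68 / 0.72 / 0.75 under weak drift and dependence (SD 0.15, coefficient 0.4) and 0.80 / 0.95 / 1.07 under strong (SD 0.25, coefficient 0.7), with 4 replicates each.

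**4. Simulation B: CRI has no effect (true HR 1).** N = 14,400, follow-up to 168 h, a binary deterioration state, and CRI in 0–2, 2–12 and 12–24 h. The fit was a piecewise-exponential proportional hazards model, with 3–4 replicates per scenario. Entries are early / mid / late HRs against no CRI yet.

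| Scenario | Fixed severity only | Plus first vital signs | Plus time-varying state |
|---|---|---|---|
| Strong entry indication, weak deterioration | 4.53 / 2.32 / 1.55 | 1.03 / 0.97 / 0.93 | 1.02 / 0.96 / 0.92 |
| Strong, persistent deterioration | 2.76 / 2.36 / 1.87 | 1.49 / 1.54 / 1.45 | 1.03 / 1.04 / 1.02 |
| Deterioration the only trigger, persistent | 1.34 / 1.38 / 1.38 | 1.25 / 1.29 / 1.30 | 1.03 / 1.03 / 1.06 |
| Deterioration from 2 h, late CRI mostly triggered by it | 1.77 / 2.16 / 1.79 | 1.17 / 1.54 / 1.39 | 0.97 / 1.03 / 0.93 |
| As above, strong entry indication | 4.16 / 2.99 / 2.51 | 1.21 / 1.44 / 1.46 | 0.99 / 0.99 / 1.01 |

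**5. Reading the tables.**

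- *Delivery.* With fixed severity only, every band in Simulation B lies above 1. Part of this is entry physiology, which first vital signs remove (first row). The rest is later deterioration, which they do not remove: with persistent moderate or strong deterioration the bands stay at about 1.15–1.55.
- *Timing.* With fixed severity only, the early/late ratio ran from 0.96 to 2.9 across all scenarios. With first vital signs it was 0.83–0.86 where late CRI was mostly triggered by deterioration, and 0.95–1.10 otherwise.
- *Control.* Including the time-varying state gave band HRs of about 0.92–1.06, the truth within simulation noise. Ordinary adjustment works here only because simulated CRI does not change later physiology. Real CRI may.

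**The case against.** A reader might infer that the planned model manufactures the hypothesised pattern, with early CRI looking better than late. The documents do not support that. With covariates like those named, Simulation A shows no gradient and Simulation B often shows early CRI looking worse. The early-better pattern mainly appears once first vital signs are in the model and late CRI is driven mostly by deterioration. The article names no such covariate and says nothing of the kind about late CRI. It attributes delay largely to slow response, transport and time in non-trauma centres, with referral distances up to 125.5 km. Neither simulation models arrival or transport delay. For a patient who arrives many hours after injury, the first hospital vital signs already reflect much of the course. This objection stands.

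The sizes also rest on unsourced inputs. The weak case of Simulation A is close to the truth, and with 4 replicates its Monte Carlo SE is roughly 0.04–0.06 on the log scale. That stands too.

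The covariate list is illustrative, joint modelling of CRI and death is among the alternatives, and an article condenses its protocol. This weakens any claim that the adjustment set is closed. It does not answer the point. The list is tied to Table 2, which has no physiology. Left truncation addresses delayed entry, and the survivor average causal effect addresses truncation by death. The joint model has no stated trigger and no stated use of measured clinical status. The article nonetheless claims valid estimates.

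Finally, hospital data come from handwritten charts with acknowledged gaps, and the article does not promise regular, time-stamped repeat vital signs. This limits the remedy.

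**Conclusion.** The concern holds in this form: the mortality model as described names no time-varying clinical status, so time-dependent confounding by indication can bias the hazard ratios for both CRI delivery and CRI timing.

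The most general effect under the named covariates is that CRI looks less beneficial, or harmful, in every band. The direction of the early-versus-late distortion is not determined. Under the assumed inputs the size can match or exceed the detectable 0.85: delivery estimates inflated by a factor of about 1.56–1.59 in Simulation A, against the 1.18 that would cancel a true 0.85, and false early/late ratios of 0.83–0.86 in some Simulation B scenarios. First vital signs reduce the bias but do not reliably remove it.

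All of this depends on deterioration both triggering CRI and predicting death. If late CRI reflects mainly transport and referral delay, the bias from deterioration would be smaller. The article gives no data to settle which applies.

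**What to change.** Keep the planned Cox model and prespecify a companion analysis beside it.

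- Divide the first 24 h into intervals whose width suits charting frequency. Among patients still untreated, model the start of CRI in each interval from the baseline covariates plus the last vital signs and consciousness score charted before that interval.
- Form stabilised, truncated inverse-probability-of-treatment weights and fit the time-dependent Cox model with them (a marginal structural Cox model). Sequential comparisons among still-untreated patients, adjusted for status at the start of each interval, would serve equally.
- Do not enter vital signs recorded after CRI as ordinary covariates. CRI can change them, and adjustment would block part of its effect.
- State that delivery and timing estimates will be read causally only if the two analyses agree. Agreement is necessary, not proof.
- Add time-dependent confounding by indication to the Limitations.

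The cost is plan wording and programming on clinical data already being abstracted, plus wider confidence intervals. The result depends on repeat charted vital signs. Where these are sparse the correction will be partial, so completeness should be reported with it.

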### Inclusion and exclusion criteria

The EpiC study will include adult patients aged 18 years and older with a clinical encounter for a traumatic injury at one or more of our 10 study sites. Eligible patients will meet one of the following criteria: (1) arrive and/or depart by WCG EMS to/from a participating site, (2) transported via WCG EMS with initial signs of life or receive prehospital resuscitation care, but die in the ambulance prior to hospital arrival, (3) were alive at the time of the EMS call but were deceased upon their arrival, or (4) emergency center walk-ins. Those under the age of 18 years, prisoners, injury onset > 24-h prior to arrival at first study site, bites, stings, other forms of envenomation, toxicologic injuries, drownings, patients who are found deceased on scene, and/or patients transported via private EMS (non-WCG EMS) will be excluded.

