2^O^—30-day in-hospital mortality	All-cause mortality at any point during the hospital stay	Time-to-event	Hospital or Pathology
2^O^—Non-resuscitative surgical interventions	Post-injury interventional procedures such as fasciotomies, limb amputation, and laparotomies	Binary	Hospital
2^O^—Secondary infections	Post-injury infections such as wound infections, pneumonia, and sepsis	Binary	Hospital
2^O^—Organ failure	Organ failure will be assessed by individual organ (acute kidney injury, coagulopathy, and acute lung injury) and by a composite multiple organ failure score such the SOFA score up to 7-days	Continuous	Hospital

1^O^ = primary exposure or outcome; 2^O^ = secondary exposure or outcome; Data Source: EMS data is abstracted from WCG EMS Electronic Patient Care Reports, hospital data is abstracted from handwritten medical charts, and pathology data is abstracted from handwritten postmortem/autopsy reports from the Forensic Pathology Service of South Africa. EMS = Emergency Medical Services, ISS = Injury Severity Score, AIS = Abbreviated Injury Scale (anatomical score), SOFA = Sequential Organ Failure Assessment

The primary outcome of mortality will be defined as time to ambulance death or in-hospital death within 7 days of injury. The definition of examining mortality within 7 days was previously selected by a 20-person expert trauma panel to be the ideal duration to assess deaths for a study focused on the effects of early trauma resuscitation [52]. A study of three trauma-focused randomized controlled trials in urban U.S. settings have demonstrated that most hemorrhagic deaths occur in hospitals and within 6 h of patient encounter [51]. However, in our setting we examine a longer window since early deaths are more likely to occur at the scene due to the higher prevalence of penetrating injuries and fewer ambulance resources, and consequently later deaths will likely occur post-EMS transfer and hospital arrival. We will define the secondary outcomes of 24-h and 30-day mortality as time to in-ambulance or in-hospital mortality from injury. Other secondary outcomes include patients’ morbidity and need for operative interventions (those that are not considered damage control surgery), secondary infections (including wound infections, pneumonia, and sepsis), and organ failure (defined with the Sequential Organ Failure Assessment (SOFA) Score [53, 54]).

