## Limitations

There are several limitations to this study design and methodology. First, the chart review and abstraction approach present challenges such as missing data and difficulty deciphering handwritten records. To mitigate this, the study will continuously monitor data completeness and provide ongoing feedback to data collectors. Second, EpiC data will be prone to selection bias as not all injured individuals seek medical attention, and because the study population is limited to those seeking care at specified facilities [76]. Additionally, EpiC does not collect information for individuals that die during non-EMS transport to the hospital, which will potentially exclude individuals with extremely severe injuries from our analysis and will limit the generalizability of results to this population. Further, EpiC began enrollment during the COVID-19 pandemic when trauma caseloads across South Africa and in the Western Cape Province were reduced by up to 50% [36], which can result in the reporting of rates that are lower compared to pre-COVID periods.

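### Delayed entry is built into the cohort, but the left-truncated Cox model is only an optional alternative; read naturally, the main mortality model is biased towards no CRI benefit

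*Protocol article*

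**What the plan says.** **Outcome clock.** Under Variables, outcomes, and study measures, the primary outcome is "time to ambulance death or in-hospital death within 7 days of injury". The 24-h and 30-day mortality outcomes are also timed from injury.

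**Exposure clock.** Under Assessing association with mortality outcomes, the interest is in "the effect of receiving CRI during different time periods post-injury (e.g., 0–2, 2–12, > 12 h").

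**Who can be observed.** Inclusion criterion (3) admits patients who "were alive at the time of the EMS call but were deceased upon their arrival". Patients found dead at the scene are excluded, as are those with "injury onset > 24-h prior to arrival at first study site". Walk-ins are eligible, but the Limitations section states that "EpiC does not collect information for individuals that die during non-EMS transport to the hospital".

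**Model.** The main analysis is "Multivariable Cox proportional hazards models with a time-dependent covariate for CRI". The text then adds: "We will consider alternative model specifications as necessary, including a left truncated Cox proportional hazards model". Joint modelling and a survivor average causal effect stand in the same list. No criterion is given for when any of these would be used.

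**The concern.** A patient who enters 3 h after injury could not have appeared in the data as a death at 1 h, because a death at 1 h would have kept that patient out of the cohort. If risk sets open at injury, the patient still counts at 1 h as untreated and at risk. The time-dependent covariate deals with immortal time between entry and CRI. It does nothing for the interval between injury and entry.

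The extra person-time goes to the untreated state and carries no deaths. The untreated hazard is understated and the CRI hazard ratio rises, so a real benefit is masked. Early mortality is the most exposed, because the surplus person-time lies in the first hours.

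The Limitations section treats the missed deaths as selection bias and a limit on generalizability. It does not treat them as a risk-set problem in the main model. Delayed entry follows from the eligibility criteria and is known in advance, so there is no reason to leave its handling to a later judgement. If the two models disagree, choosing between them after seeing the data is an avoidable analytic choice.

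**Working it through.** **1. Reproduce the protocol's figure.** The Power calculation section gives 14,400 cases, 10% 7-day mortality, 30% treated within 2 h, two-sided alpha 0.05, 80% power and a detectable hazard ratio of 0.85.
- Expected deaths: 14,400 × 0.10 = 1,440.
- Schoenfeld events needed: (1.960 + 0.842)² / (0.30 × 0.70 × (ln 0.85)²) = 1,416 after rounding up.
- Power with 1,440 deaths: Φ(√(1,440 × 0.21) × |ln 0.85| − 1.960) = Φ(17.39 × 0.1625 − 1.960) = 80.7%. The detectable hazard ratio is 0.851.

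The stated figure reproduces, with almost no reserve.

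**2. Simulate the bias.** No closed formula fits. The protocol gives neither the entry-delay nor the death-time distribution, so these inputs are assumptions:
- death hazard per hour 0.012 (0–2 h), 0.004 (2–6), 0.0012 (6–24), 0.0004 (24–72), 0.00015 (72–168);
- entry delay lognormal, log SD 0.9;
- CRI at entry plus a lognormal lag (median 1.5 h, log SD 1.0), with 30% never treated;
- true hazard ratio 0.85, and only patients alive at entry kept.

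Each cohort was analysed by a Cox model with time-dependent CRI, with the risk set opened at injury or at entry. Ranges cover repeated independent runs.

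| Median entry delay | CRI within 2 h | 7-day HR, opened at injury | 24-h HR, opened at injury | HR with delayed entry (both horizons) |
|---|---|---|---|---|
| 0.5 h | 30% | 0.87 | 0.88–0.90 | 0.84–0.86 |
| 1 h | 20% | 0.90 | 0.94–0.95 | 0.84–0.85 |
| 2 h | 10% | 0.94–0.96 | 1.04–1.07 | 0.83–0.85 |

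Only the first row matches the protocol's 30% treated within 2 h. Simulated 7-day mortality is 6–8%, below the protocol's 10%.

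**3. Vary the shape.** A second simulation used 14,400 enrolled, 10% mortality, Weibull death times (shape 0.3, 0.5 or 1.0), true hazard ratio 0.85 and 35–39% treated within 2 h.

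| Entry delay | Overall HR, opened at injury | HR for CRI at 0–2 h, opened at injury | Overall HR, delayed entry |
|---|---|---|---|
| Median 1 h, 1% over 6 h | 0.86–0.91 | 0.87–0.92 | 0.85–0.86 |
| Median 1.3 h, 15% over 6 h | 0.90–1.11 | 0.91–1.13 | 0.85–0.86 |

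With a true hazard ratio of 1.00, opening at injury gave 1.02–1.06 (short delays) and 1.06–1.32 (spread delays). Delayed entry gave 1.00–1.01.

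**4. Translate to power.** With 1,440 deaths and 30% exposed:
- HR 0.87: Φ(17.39 × 0.1393 − 1.960) = Φ(0.46) = 68%.
- HR 0.90: Φ(17.39 × 0.1054 − 1.960) = Φ(−0.13) = 45%.

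This is approximate. The formula treats exposure as fixed at baseline, as the protocol's own calculation does.

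**The case against.** **The protocol never says that risk sets open at injury.** This stands. Injury as the time scale is compatible with delayed entry, and the same section describes the cohort as people alive when help is first sought, so the authors know the entry condition. A reader might take it as settled that the main model omits delayed entry. The text supports this only as an inference, though a fair one: a left-truncated model listed as an alternative implies that the main model is not left-truncated.

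**The remedy is already named, and its coding belongs in an analysis plan.** This stands in part. Coding details are no finding against a condensed article. But the article does more than omit a detail: it names the main model and gives the needed correction provisional status.

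**Large biases are not what the protocol's figures imply.** This stands. A reader might infer from the longer-delay rows that the bias erases or reverses the CRI effect. Those rows have 20% or 10% treated within 2 h, or assume that 15% enter after 6 h. The 24-h limit is an eligibility cap and says nothing about typical delay.

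**Starting the clock at the EMS call may not be enough.** This also stands. Patients found dead at the scene are excluded, so part of the interval from call to contact may still be immortal.

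**Conclusion.** The concern holds in direction, with a modest size under the assumptions closest to the protocol. If the main model is fitted as it naturally reads, the CRI hazard ratio is biased upward and benefit is masked. With about 30% treated within 2 h, in the first simulation model, 0.85 becomes about 0.87 at 7 days and 0.88 at 24 h. Planned power of 80% falls to roughly 68%. Across the other assumed delays and death-time shapes, the 7-day value ran from 0.86 to 1.11. The upper end depends on delay distributions that the documents do not give and is not a prediction for this study. Opening the risk set at entry removed the shift, apart from simulation error, in the scenarios tabulated.

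This should be fixed, with medium confidence: the direction is firm, while the opening of the risk set at injury is inferred and the size is assumed. Left truncation does not remove confounding by indication, so the corrected hazard ratio would still need that caveat.

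**What to change.** - Make the primary mortality model a Cox model on the injury time scale with delayed entry and time-dependent CRI. Apply the same risk-set rule to 24-h and 30-day mortality.
- Keep the model without truncation as a sensitivity analysis only.
- Define entry by route. For walk-ins it is arrival at the first study site. For EMS patients it is either the call or the EMS contact. Inclusion criterion (3) and the exclusion of patients found dead at the scene must first be reconciled, because together they decide which applies.
- Confirm that the chosen entry time is recorded. The protocol says that key dates and times are collected but does not name the EMS call time.

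If the time stamps exist, the cost is a sentence in the plan and an entry-time argument in the model call, with somewhat smaller early risk sets. If the EMS call or contact time is not abstracted, it must be added to data collection. Patients without an entry time would fall under the existing missing-data rules.
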